### Statistical methods

2.13

Study analyses will follow an intention-to-treat analysis plan using multiple imputation to account for missing data. To understand baseline variation and ensure experimental rigor, baseline scores on all psychosocial and occupational outcomes will be checked for between arm consistency using one-way analysis of variances (ANOVAs).

For the primary outcome (changes in OLBI burnout scores), between group variations (i.e., reductions in burnout between arms) will be examined using a 3 (blended, self-guided, active attention control) x 2 (baseline, 3 months post-treatment) mixed model ANCOVA controlling for gender, age, profession, and regionality and explored with pairwise comparisons. Identically formatted mixed model ANCOVAs will be used to analyse the secondary aims and outcomes of between arm and baseline to post-treatment and 3-month post-treatment differences in DASS (anxiety and depression), WSAS (psychosocial functioning), WHO-HPQ (workplace participation), and TIS-6 (attrition intention). The secondary aim and outcomes of comparing service acceptability between arms will be analysed using one-way ANOVAs.

If primary outcome data (i.e. OLBI at 3 months post-treatment) is unavailable for more than 5% of participants from the intention-to-treat population then exploratory and sensitivity analyses will be conducted. The following exploratory analyses of missing primary outcome data will be conducted to inform missingness categorisation and missing data handling: comparing proportion of attrition between arms, reasons for withdrawal, and baseline characteristics between those with and without the primary outcome. Best-worst and worst-best case sensitivity analyses will also be conducted alongside sensitivity analyses using last observation carried forward. Based on the results of these exploratory and sensitivity analyses, either complete case analysis or multiple imputation with 100 imputed data sets of the primary outcome will be conducted.

To examine the cost-effectiveness of blended (therapist-guided) Navigating Burnout, direct costs of the blended care arm will be quantified (computed as actual service delivery costs incurred by BDI) alongside indirect costs such as lost productivity of recipients due to use of the intervention (computed as average role wage multiplied by time taken out of work where sessions are attended during work hours, then annualised and adjusted for average FTE). Due to a lack of standardised and established estimates of the economic cost of burnout using commonly used measures, the benefits of blended Navigating Burnout will be compared against the value of improvements in occupational outcomes (WHO-HPQ; TIS-6), computed as average role wage multiplied by additional work engagement over the period of measurement, then annualised and adjusted for average FTE. Comparisons of these costs and benefits between treatment arms will provide an estimate of the net benefit and cost-effectiveness of blended Navigating Burnout. One-way and multi-way sensitivity analyses will be performed on assumptions in the model, such as cost estimates of lost productivity due to treatment and the relationship between turnover intention and actual turnover.

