### Participants

2.2

Individuals will be eligible to participate in the trial if they satisfy all of the following criteria.•registered doctor currently practising in Australia;•able to read and speak English fluently;•current experience of self-reported burnout;•able to access the internet in a private location on a device suitable for viewing websites and attending telehealth consultations; and•able to attend telehealth consultations during Monday to Friday business hours (9.00–17.00).

Individuals will be excluded from trial participation if they satisfy any one or more of the following criteria.•current diagnosis of severe mental illness that requires more specialist support (e.g., bipolar disorder, schizophrenia, etc.);•current engagement with person-to-person psychological therapy (e.g. cognitive-behavioural therapy);•DASS-21 symptom scores in the Severe or Extremely Severe ranges for anxiety or depression during screening; or•report suicidal ideation or problematic alcohol or drug use during screening.

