Following consent, an online screening survey will be completed through REDCap. It will ask potential participants to confirm the inclusion criteria, as well as complete a modified version of the DASS-21 to confirm the absence of exclusion criteria. The modified DASS-21 includes two risk-related items addressing suicidal ideation (“I had thoughts that I would be better off dead, or thoughts of hurting myself in some way”) and problematic use of alcohol or drugs (“I found it difficult to control my consumption of alcohol or other drugs”) rated on the same 0–3 scale as the other questions in the DASS-21 ranging from “Did not apply to me at all” to “Applied to me very much or most of the time”. Potential participants are ineligible to participate if they report DASS-21 symptom scores in the Severe or Extremely Severe ranges for anxiety (DASS-21 anxiety subscale score >7) or depression (DASS-21 depression subscale score >10) or report suicidal ideation or problematic alcohol or drug use (score >1 on respective questions). If a person does not meet the inclusion criteria, they will be notified by a message within the online survey. Branching logic will be used to present the participant with the relevant reason(s) that they were not eligible and, where relevant, provide links to crisis services and/or TEN where they may find support. If a person reports suicidal ideation or problematic alcohol or drug use during screening (rating of “Often” or “Almost Always” on screening items addressing these criteria) a clinical psychologist (PB or MB) will contact the participant directly by email to direct the person to appropriate supports.

To confirm that all participants are registered doctors following successful online screening and prior to data collection, potential participants' name, postcode, and profession will be checked against the Australian Health Practitioner Regulation Agency (AHPRA) database – a publicly available list of registered health professionals in Australia. In the event that a participant's registration cannot be verified, they will be contacted by email for clarification.

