### Procedure

2.8

Eligible participants will complete baseline surveys (demographics and psychometrics) before random allocation to self-guided, blended, or active attention control. All arms will access their allocated treatment over 10 weeks. Participants will complete follow-up surveys (psychometrics, service acceptability questions) immediately post-treatment, and again three months post-treatment to assess maintenance of therapeutic effects.

Following completion of the 3 months post-treatment survey, or once participants are considered lost to follow-up at the 3 months post-treatment timepoint, participants allocated to the self-guided or active attention control will be provided with information about TEN, including information on how to access the self-guided Navigating Burnout and/or person-to-person care.

Participants will complete 6 psychometric questionnaires: Oldenburg Burnout Inventory (OLBI; burnout) [22], Depression Anxiety Stress Scale (DASS-21; depression and anxiety) [23], Work and Social Adjustment Scale (WSAS; psychosocial functioning) [24], World Health Organisation Health and Work Performance Questionnaire (WHO-HPQ; workforce participation) [25], Turnover Intention Scale-6 (TIS-6; workforce attrition) [26], and Client Satisfaction Questionnaire (CSQ-8; intervention acceptability) [27]. To further assess acceptability, bespoke questions regarding the self-reported usage and acceptability of Navigating Burnout will also be employed, alongside open-ended questions about participants’ experiences with their allocated treatment and their experiences of burnout.

The OLBI, DASS-21, WSAS, WHO-HPQ, and TIS-6 will be completed at baseline, post-treatment, and 3 months post-treatment, while the CSQ-8 and service acceptability questions will only be completed at the post-treatment timepoint. See Table 1 for an overview of measures employed across trial timepoints. Regular safety audits (2–3 times per week) of the post-treatment and 3 months post-treatment surveys will be conducted, and any responses indicative of distress or suicidal ideation will be reported to PB. If a participant consented to a check-in call related to indicators of distress or suicidal ideation, a clinical psychologist (PB or MB) will contact the participant immediately.

**Table 1 tbl1:** Measures employed across trial timepoints.

Measure	Baseline	Post-treatment	3 months post-treatment

Demographics	X		
OLBI	X	X	X
DASS-21	X	X	X
WSAS	X	X	X
WHO-HPQ	X	X	X
*TIS-6*	X	X	X

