### Primary outcome

2.9

The primary outcome will be self-reported burnout, as measured by the OLBI, with the primary endpoint being 3 months post-treatment.

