### Secondary outcomes

2.10

The secondary outcomes will be.•burnout (OLBI) at post-treatment•self-reported anxiety, depression, and stress (DASS-21) at post-treatment and 3 months post-treatment;•psychosocial functioning (WSAS) at post-treatment and 3 months post-treatment;•workforce participation (WHO-HPQ) at post-treatment and 3 months post-treatment;•workforce attrition intentions (TIS-6) at post-treatment and 3 months post-treatment;•service acceptability (CSQ-8) at post-treatment.

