## Limitations

6

The self-guided digital Navigating Burnout program is currently publicly available through TEN without need for registration or an account. This decision followed the broad rationale behind TEN's development to reduce barriers to help-seeking and minimise health professionals' concerns around confidentiality. As such, there is a risk of contamination in the active attention control arm whereby participants could potentially access Navigating Burnout outside of the scope of the trial. To minimise the risk of contamination, references to TEN and Navigating Burnout will be omitted from recruitment materials and the PISCF.

Due to the nature of the funding for the trial, the participant population is limited to registered doctors. While this may limit the generalisability of findings to other health professionals, health professionals often share similar occupational environments and vulnerability to burnout. As such, there is a strong rationale for the applicability of findings to other health professional groups. A final limitation is that this intervention addresses the individual factors of burnout but does not directly address the more substantial systemic causes which, while beyond the scope of our study, urgently require greater attention.

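### The primary 3 x 2 mixed ANCOVA uses baseline OLBI as an outcome level instead of a covariate: it is valid, but in large samples never more precise than adjusting for baseline

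*Protocol article*

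**What the plan says.** All references are to the protocol article.

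- **Primary model (2.13 Statistical methods).** Three arms "x 2 (baseline, 3 months post-treatment) mixed model ANCOVA controlling for gender, age, profession, and regionality", followed by pairwise comparisons. Baseline OLBI is one of the two time levels and is not among the covariates.
- **Quantity compared (2.13).** "For the primary outcome (changes in OLBI burnout scores), between group variations (i.e., reductions in burnout between arms) will be examined". This points to the arm-by-time term.
- **Endpoint (2.9 Primary outcome).** OLBI, "with the primary endpoint being 3 months post-treatment".
- **Data collected (2.8 Procedure).** "The OLBI, DASS-21, WSAS, WHO-HPQ, and TIS-6 will be completed at baseline, post-treatment, and 3 months post-treatment". The middle measurement is not a level of the primary model.
- **Secondary outcome (2.10).** The list opens with "burnout (OLBI) at post-treatment". The secondary mixed models in 2.13 name DASS, WSAS, WHO-HPQ and TIS-6, but not OLBI.
- **Profession.** Entry requires a "registered doctor currently practising in Australia" (2.2 Participants), and section 6 (Limitations) says that "the participant population is limited to registered doctors". The word is used for the registration category in 2.5, where "postcode, and profession will be checked against the Australian Health Practitioner Regulation Agency".

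**The concern.** With two time points, the arm-by-time term of a mixed ANOVA is the between-arm difference in mean change. A change score subtracts the whole baseline value, which amounts to fixing the regression slope of follow-up on baseline at 1. Baseline-adjusted ANCOVA estimates that slope. Unless the true slope is 1, the change score carries avoidable noise.

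The listed covariates do not fill the gap. Gender, age and regionality do not change between visits, so they cancel from a within-person change unless they are crossed with time, and the article does not say that they are. Profession takes one value in this trial.

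What is at stake is the precision of the main result: a wider confidence interval than the collected data allow, in a trial sized for 80% power. The same model form is carried over to DASS, WSAS, WHO-HPQ and TIS-6.

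**Working it through.** **Inputs.** From 2.12 (Sample size): alpha 0.05, power 0.80, f = 0.25, 53 evaluable per arm, 30% attrition. From 2.13: the model above. Assumed, because the article gives neither: the correlation rho between baseline and 3-month OLBI, and the two SDs, s1 (baseline) and s2 (3 months).

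**Step 1: the plan's own figure.** For a three-group omnibus test with non-centrality f² x N and N - 3 error degrees of freedom, 80% power needs N = 158, which is 53 per arm. At N = 159 power is 0.805. The 53 reproduces. With two time levels the arm-by-time test has the same degrees of freedom.

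**Step 2: the two variances, per participant.**

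- Change score: s1² + s2² - 2·rho·s1·s2
- Adjusted for baseline: s2²(1 - rho²)
- Difference: s1² - 2·rho·s1·s2 + rho²·s2² = (s1 - rho·s2)²

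A square cannot be negative. In large samples, where the cost of estimating one slope is negligible, the change score is therefore never the more precise of the two.

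**Step 3: equal SDs (s1 = s2 = 1).** The ratio is (1 - rho²) / [2(1 - rho)] = (1 + rho)/2, so the variance given up is (1 - rho)/2.

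| rho (assumed) | Change score | Adjusted | Ratio | Given up | 53 per arm x ratio |
|---|---|---|---|---|---|
| 0.2 | 1.60 | 0.96 | 0.60 | 40% | 32 |
| 0.4 | 1.20 | 0.84 | 0.70 | 30% | 38 |
| 0.5 | 1.00 | 0.75 | 0.75 | 25% | 40 |
| 0.6 | 0.80 | 0.64 | 0.80 | 20% | 43 |
| 0.7 | 0.60 | 0.51 | 0.85 | 15% | 46 |
| 0.8 | 0.40 | 0.36 | 0.90 | 10% | 48 |
| 0.9 | 0.20 | 0.19 | 0.95 | 5% | 51 |

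The last column, rounded up, applies only if f = 0.25 is scaled to the change score, which 2.12 does not say. A simulation with 53 per arm and 4,000 replications gave ratios of 0.70, 0.75, 0.82 and 0.88 at rho 0.4, 0.5, 0.6 and 0.7, close to the formula.

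**Step 4: unequal SDs.** Selecting participants for current burnout may narrow the baseline spread. With s1 = 0.8 and s2 = 1:

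- rho 0.4: change 0.64 + 1 - 0.64 = 1.00; adjusted 0.84; given up 16%
- rho 0.5: change 0.64 + 1 - 0.80 = 0.84; adjusted 0.75; given up 11%
- rho 0.7: change 0.64 + 1 - 1.12 = 0.52; adjusted 0.51; given up 2%

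If the baseline spread is wider instead (s1 = 1.2), the loss is 0.64/1.48 = 43% at rho 0.4 and 0.25/0.76 = 33% at rho 0.7.

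**Step 5: the other two features.**

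- *Constant profession.* A model fitted with and without a constant covariate gave identical standard errors and residual degrees of freedom (154 in both). The cost is 0%.
- *Post-treatment OLBI left out of the primary model.* With complete 3-month data the cost is 0%. With 30% missing at 3 months it ranges from 0% to about 10%, depending on how many of those missing gave a post-treatment score and on the assumed correlations between visits.

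**The case against.** The strongest reply is that nothing here is wrong. Randomisation makes the comparison of change unbiased, and preferring ANCOVA is a preference. The first part stands: a reader might infer that the planned test is biased or invalid, and it is not. But the efficiency result follows from the algebra whatever the SDs and correlation, and the article fixes this model itself instead of leaving it open.

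Several stronger readings should be resisted.

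- **A loss of 15-30% as a fact about this trial.** That range needs rho between 0.4 and 0.7 and equal SDs. The article supports neither assumption, and plausible alternatives run from 2% to over 40%.
- **All three features lose information.** The calculated loss in Steps 3 and 4 comes entirely from the handling of baseline. The constant covariate costs nothing.
- **Participants with a post-treatment but no 3-month score are wasted.** Section 2.13 provides for multiple imputation and a last-observation-carried-forward sensitivity analysis. Nothing bars the post-treatment score from either, and the content of an imputation model is commonly left to a fuller document.
- **The test is the arm main effect, diluted by the baseline visit.** Section 2.13 speaks of changes and reductions, which supports the arm-by-time term.

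It may also be said that the covariates could be crossed with time, or that baseline means could be constrained equal across arms, which would recover most of the precision. The article states neither. Profession may have been meant as specialty or role, but the text does not say so.

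**Conclusion.** The point holds as one of efficiency and clear specification. As written, the primary test is a change-score comparison that is valid under randomisation but in large samples never more precise than adjustment for baseline OLBI. With equal SDs the variance given up is (1 - rho)/2, or 15-30% for rho 0.7 down to 0.4 and 5-10% for rho 0.8-0.9. With a baseline SD 0.8 of the 3-month SD it falls to about 16% at rho 0.4 and 2% at rho 0.7. The size in this trial cannot be settled from the article; the direction can.

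Two separate drafting points stand: profession is constant as written, at no cost in precision, and the post-treatment OLBI listed in 2.10 is not named among the analyses in 2.13. The whole is best classed as a free improvement.

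**What to change.** Replace the primary model in 2.13 with a mixed model for OLBI at post-treatment and 3 months, as follows.

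- **Terms:** pre-randomisation baseline OLBI, arm, visit, arm x visit, baseline x visit, age, gender and regionality, with unstructured covariance. Saying pre-randomisation also settles the role of the repeat OLBI that 2.8 collects in the blended arm when the first consultation is delayed.
- **Primary estimate:** the blended minus self-guided difference at 3 months, with its 95% CI.
- **Post-treatment OLBI:** report the contrasts at that visit from the same model as the secondary outcome in 2.10.
- **Missing data:** keep multiple imputation or an equivalent. A model of follow-up scores conditional on baseline would otherwise drop participants with no follow-up score from the intention-to-treat analysis.
- **Other outcomes:** use the same form for DASS-21, WSAS, WHO-HPQ and TIS-6.
- **Profession:** delete it, or define it as specialty or career stage if that is collected.

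The OLBI data are already collected, and no visits or participants are added. The cost is a dated, documented change to the stated primary analysis of a registered trial.

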### Trial design

2.1

We will conduct a three-arm RCT to compare the effectiveness, acceptability, and cost-effectiveness of Navigating Burnout in reducing burnout among doctors across three delivery modalities.

Medical doctors (n = 207) will be randomly allocated to receive either [1] a blended version of the program combining the digital Navigating Burnout resources with five fortnightly telehealth sessions with a clinical psychologist [2]; a digital-only, self-guided version of the Navigating Burnout program; or [3] an active attention control where participants will be provided with digital self-care psychoeducation via email each fortnight. Across all conditions the treatment phase across will last 10 weeks.

We will measure self-reported burnout, psychosocial wellbeing, workforce engagement, and workforce attrition intentions before treatment, immediately after treatment, and 3 months after completing treatment (see Fig. 1 for trial design). This design will enable us to examine the effectiveness and acceptability of blended care Navigating Burnout compared to self-guided Navigating Burnout, as well as to examine the effectiveness of self-guided Navigating Burnout relative to an appropriate control.

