### Randomisation

2.6

Eligible participants will be randomly allocated to the blended care, self-guided, or active attention control arm using a 1:1:1 ratio. Randomisation will be completed following completion of baseline outcomes.

A randomisation list in a Microsoft Excel file will be prepared in advance using a random number generator using block sizes of 6, 9, and 12. When a participant is ready to be randomised, the list holder will be contacted, and the allocation provided. Participants will be informed which treatment they have been randomly assigned via email.

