### Sample size

2.12

We will enrol 207 participants to complete the trial. This sample size is sufficient to examine the primary outcome using repeated measures ANOVA of whether the blended care version of the Navigating Burnout program leads to significantly lower burnout between baseline and 3 months post-intervention compared to self-guided treatment based on a power analysis (α = .05 and power = 0.80) using a conservative medium effect size of f = 0.25 between groups estimating a sample size of 53 per arm (WebPower). As there is limited literature on the effect of blended care treatments for burnout relative to self-guided digital psychotherapeutic programs, a medium effect size of f = 0.25 was chosen as a minimum clinically meaningful effect [28]. Accounting for a conservative estimate of 30% attrition based on previous research health professionals [19], 69 participants are required in each arm leading to a total sample size of 207.

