## Results

4

It is anticipated that this trial will see improvement in burnout symptoms from baseline to 3 months post-treatment in both intervention arms (blended care and self-guided), with a more significant effect in the blended care arm. It is also anticipated that the trial will lead to improvements in the secondary aims and outcomes (anxiety and depression, psychosocial functioning, workforce participation, and workforce attrition intention) from baseline to 3 months post-treatment.

The active attention control is expected to be clinically inert (i.e. have no measurable effects on burnout outcomes, or the psychosocial and workforce secondary outcomes). However, the use of self-care materials by participants in the control arm may lead to some incidental improvements.

Navigating Burnout is expected to evidence high service acceptability among participants, and to be capable of implementation in a cost-effective manner.

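### The contrast the trial says it is sized for, blended versus self-guided, is not carried into the primary analysis as the deciding test

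*Protocol article*

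**What the plan says.** The endpoint is settled: section 2.9 (Primary outcome) gives OLBI burnout at 3 months post-treatment. The comparison is described in several places.

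- **Section 2.12 (Sample size)** presents the primary question as "whether the blended care version of the Navigating Burnout program leads to significantly lower burnout between baseline and 3 months post-intervention compared to self-guided treatment". The calculation is a "power analysis (α = .05 and power = 0.80") with a "conservative medium effect size of f = 0.25 between groups estimating a sample size of 53 per arm (WebPower"). After attrition, "69 participants are required in each arm leading to a total sample size of 207".
- **Section 2.13 (Statistical methods)** analyses the primary outcome with three arms by two times, in a "mixed model ANCOVA controlling for gender, age, profession, and regionality and explored with pairwise comparisons".
- **Section 2.1 (Trial design)** gives two purposes: blended against self-guided, "as well as to examine the effectiveness of self-guided Navigating Burnout relative to an appropriate control".
- **Section 2.6 (Randomisation)** allocates "using a 1:1:1 ratio".

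Section 2.13 does not say which test decides the primary outcome, how many pairs are compared, whether the pairs depend on the omnibus result, or whether they are adjusted.

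**The concern.** The question in section 2.12 involves two arms; the test in section 2.13 involves three. A three-arm test is significant when any arm differs enough from the others, so a weak control arm can produce it alone. The pair that section 2.12 calls the question appears in section 2.13 only as one of several follow-up comparisons.

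This affects what the trial can conclude. The Discussion makes adding the program to TEN's person-to-person care depend on acceptability and therapeutic benefit of the blended format. The psychologist sessions are what blended care adds to the digital program, and only blended versus self-guided isolates them. With no deciding contrast in the analysis section, a positive omnibus driven by the control arm could be reported as the primary result while the question about the sessions is unanswered, or answered in the negative.

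**Working it through.** **Inputs.** From section 2.12: α = 0.05, power 0.80, f = 0.25, 53 per arm, 69 per arm after 30% attrition. From sections 2.6 and 2.13: three equal arms. For two equal groups d = 2f, so f = 0.25 is d = 0.50 on the analysed score. Completers per arm if 30% are lost: 0.70 × 69 = 48.3, taken as 48.

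**Step 1. Reproduce 53 per arm.** For k groups and N participants in total, λ = f²N, and power is the chance that a noncentral F with k − 1 and N − k degrees of freedom exceeds the 5% critical value.

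| Test | Per arm | N | λ = 0.0625 × N | Power |
|---|---|---|---|---|
| Three-group omnibus | 52 | 156 | 9.75 | 79.7% |
| Three-group omnibus | 53 | 159 | 9.94 | 80.5% |
| Two-arm contrast | 48 | 96 | 6.00 | 67.9% |
| Two-arm contrast | 53 | 106 | 6.63 | 72.2% |
| Two-arm contrast | 64 | 128 | 8.00 | 80.1% |

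The stated 53 is the three-group figure (52.4 rounded up). The two-arm contrast named in the text needs 64.

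**Step 2. Could a correlation explain 53 for two arms?** A two-group repeated-measures between-group calculation gives 53 if the within-person correlation is about 0.65, but the article states none. If instead the 0.50 is a difference in SD units of the 3-month score and change is analysed, the effective size is d = 0.50/√(2(1 − ρ)). At 53 per arm, power is then 58% for ρ = 0.3, 72% for ρ = 0.5 and 91% for ρ = 0.7. The power of the named contrast therefore depends on an unstated assumption.

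**Step 3. Can the omnibus be positive without a blended versus self-guided difference?** Simulation with 53 per arm, one normal score per participant (SD 1), pooled variance and two-sided 0.05. Means are relative to control, negative being better.

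| Blended, self-guided, control | Omnibus significant | Omnibus significant and blended v self-guided not (share of all trials) |
|---|---|---|
| −0.5, −0.5, 0 | 75% | 71% |
| −0.5, −0.25, 0 | 62% | 39% |

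In the first row there is no true difference between the programs, so the non-significant pair is the right answer to the question in section 2.12, yet the three-arm test is positive. In the second row a real difference of 0.25 SD usually goes undetected.

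**Step 4. False positives over the three pairs.** Simulation of 1,000,000 trials with no true differences, 53 per arm:

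- pairs tested only after a significant omnibus: 5.0%;
- all three pairs ungated and unadjusted: 12.2%;
- ungated and unadjusted, only the two contrasts named in section 2.1: 9.1%.

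**The case against.** The other side has good points, and several stand.

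- **A reader might infer three unadjusted tests and a 12% chance of a false primary claim.** The article does not support that. It gives no number of pairs, does not call them unadjusted, and does not say they run whatever the omnibus shows. A three-arm model followed by pairwise exploration reads at least as naturally as a gated procedure, which with three arms holds the rate at 5%. Adjustment rules are also commonly left to a SAP, which is not shown here. The 12% is only the upper end of a conditional range.
- **A reader might infer that the arm main effect could decide the trial.** Section 2.13 describes the primary outcome as change in OLBI and the between-group question as a comparison of reductions across arms. That points to the arm-by-time term.
- **A reader might infer that within-arm improvement would count as success.** Section 4 does look forward to burnout falling from its baseline level under each program, and falling furthest with blended care, but this is an expectation, not a decision rule. The planned analysis is between arms.
- **Two aims in section 2.1 are not a contradiction.** A three-arm trial can serve both, and section 2.12 attaches the primary outcome to one of them.

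The mismatch between sections 2.12 and 2.13 is untouched by these points. It is not an omission that a SAP could excuse: the article states a two-arm question, a three-arm test and a sample size that matches the three-arm test.

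**Conclusion.** The point holds in this form: the primary contrast is named in section 2.12 but not made the deciding test in section 2.13, and the stated sample size fits the omnibus test, not the named contrast.

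At 53 per arm, a positive omnibus without a significant blended versus self-guided result occurs in 71% of trials when both programs beat control equally by 0.5 SD, and in 39% with benefits of 0.5 and 0.25 SD. Power for the named contrast at d = 0.50 on the analysed score is 72% at 53 per arm and 68% at 48, against the stated 80%. The error rate over three pairs lies between 5% and about 12%, depending on a rule the article does not give.

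These figures assume normal scores with equal variance and ignore covariates and imputation. The power figures give no credit for baseline correlation beyond what is built into the analysed score. The scenario percentages depend on the assumed means and illustrate the problem; they do not predict the trial's result.

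**What to change.** **Section 2.13.** Name the blended minus self-guided difference in OLBI change from baseline to 3 months (the arm-by-time contrast) as the single primary test at two-sided 0.05. State that a significant omnibus alone does not make the trial positive. Make self-guided versus control and blended versus control secondary.

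If error over all three contrasts is to be held at 0.05, there are two routes:

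- Test the two secondary contrasts only after the primary one is significant. This is enough with three arms: if blended and self-guided truly differ, at most one of the other two equalities can be true; if they do not, any false claim must first pass the 5% primary test. The price is that self-guided versus control gets no confirmatory test when the primary contrast fails.
- Apply Holm across all three. The primary contrast may then face α = 0.05/3, where its power at d = 0.50 and 53 per arm is 56%.

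Leaving the primary contrast ungated and putting only the other two behind the omnibus would not do it: the three-contrast rate is then about 7.5%.

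**Section 2.12.** Restate the power for blended versus self-guided at the planned numbers, giving any assumed baseline correlation.

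**Cost.** A few sentences, made before unblinding. A significant omnibus or another pair could no longer be presented as the main finding, and the restated power may be less favourable than 80%. Reaching 80% at d = 0.50 without credit for correlation would take 64 evaluable participants per arm.
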